## Abstract

**Background:**

The present developments in colon surgery are characterized by two innovations: the introduction of the laparoscopic operation technique and fast recovery programs such as the Enhanced Recovery After Surgery (ERAS) recovery program. The Tapas-study was conceived to determine which of the three treatment programs: open conventional surgery, open 'ERAS' surgery or laparoscopic 'ERAS' surgery for patients with colon carcinomas is most cost minimizing?

**Method/design:**

The Tapas-study is a three-arm multicenter prospective cohort study.

All patients with colon carcinoma, eligible for surgical treatment within the study period in four general teaching hospitals and one university hospital will be included. This design produces three cohorts: Conventional open surgery is the control exposure (cohort 1). Open surgery with ERAS recovery (cohort 2) and laparoscopic surgery with ERAS recovery (cohort 3) are the alternative exposures. Three separate time periods are used in order to prevent attrition bias.

Primary outcome parameters are the two main cost factors: direct medical costs (real cost price calculation) and the indirect non medical costs (friction method). Secondary outcome parameters are mortality, complications, surgical-oncological resection margins, hospital stay, readmission rates, time back to work/recovery, health status and quality of life.

Based on an estimated difference in direct medical costs (highest cost factor) of 38% between open and laparoscopic surgery (alfa = 0.01, beta = 0.05), a group size of 3×40 = 120 patients is calculated.

**Discussion:**

The Tapas-study is three-arm multicenter cohort study that will provide a cost evaluation of three treatment programs for patients with colon carcinoma, which may serve as a guideline for choice of treatment and investment strategies in hospitals.

**Trial registration:**

ISRCTN44649165.

## Background

### Usual care

The standard of care for colon carcinoma patients is changing. Traditionally operative treatment means an open resection (i.e. laparotomy) and 'conventional' patient-tailored recovery. In the last decade laparoscopic (assisted) colon surgery is introduced as a valuable alternative [1-5]. Over the last five years Enhanced Recovery After Surgery (ERAS) programs have been introduced and in many hospitals these alternatives gradually replace conventional care [6-11].

Equality of long term clinical (and oncological) effectiveness of laparoscopic surgery as well as ERAS recovery has been proven in literature [4,5,12-18]. To date however, strong evidence of cost minimization effects of these innovations is lacking.

Many hospitals are at a stage of investing large amounts in endoscopic operation theatres ('endosuites'). If laparoscopic surgery does not result in added cost effectiveness compared to open ERAS programs (or traditional open programs), future investments in endoscopic endosuites may be ill-advised. With this in mind a prospective cohort study is set up comparing traditional open, open-ERAS and laparoscopic-ERAS colon surgery.

### Health care problem

Costs of conventional open colon surgery is substantial. With approximately 9000 operations for colon carcinoma in the Netherlands annually, direct medical costs are estimated at 38.6 million euro [19].

Overall cost effectiveness studies on laparoscopic and open colon surgery have shown little differences [14,20]. This allows us to focus merely on direct medical costs accompanying laparoscopic surgery, showing an increase to 65.3 million euro for laparoscopic surgery (difference of 26.7 million euro per year). On top of these costs, hospital investments in laparoscopic operation theatres should be taken into account. Many Dutch hospitals are currently planning such investments. Reduction of time back to work (indirect non-medical costs) due to enhanced recovery from laparoscopy could compensate for these extra costs. However this cost minimization issue has never been clearly investigated.

Investment costs of ERAS recovery programs (mainly ward personnel costs and training facilities) have not been well established so far. Especially direct medical costs due to intensified activities of ward personnel should be considered. From a cost minimization point of view, reduction of hospital stay and enhanced rehabilitation to normal activity/work should equalize the increased personnel costs. This issue of presumed cost savings has not been raised so far nor evaluated.

In line with the two aforementioned cost minimization questions, a third question arises: which investment (in ERAS recovery programs, in laparoscopic operation theatres and -surgery or a combination of both) is most valuable for hospitals in near future.

## Methods/design

### Study objectives

The current study has the following two objectives:

To discern the most cost minimizing surgical peri-operative treatment program for colon cancer patients and to indicate justification or rejection of investments in these hospitals.

To supplement the lack of knowledge in literature on cost minimizing differences between the three treatment programs and to provide recommendations on further development in the operative treatment of colon carcinomas from an economic point of view.

### Study design

The Tapas-study is a multicenter prospective cohort study. Randomised Controlled Trials are considered to give the highest level of evidence. Since randomization produces the best comparable groups, which is methodological the best manner to compare the intervention group with the conventional/standard group. However, cohort studies can easily separate complex multidisciplinary treatment programs such as ERAS into time and place, preventing an important bias: the attrition bias. An attrition bias occurs when elements of the control and alternative intervention mix and hence influences outcome. This explains why studies with ERAS are often correctly designed as cohort studies and not as randomized controlled trials [21,22].

Conventional open surgery is the control exposure (cohort 1). Open surgery with ERAS recovery (cohort 2) and laparoscopic surgery with ERAS recovery (cohort 3) are the alternative exposures. Three separate consecutive time periods are used in order to prevent attrition bias. Before each new cohort starts a quality control assessment will be carried out by the expert project advisors from the research group on ERAS recovery and laparoscopic surgery.

### Primary and secondary endpoints

The primary endpoint of the Tapas-study are costs, both direct medical en indirect non medical costs. Direct medical costs are defined as the total costs of medical resources used for diagnostics, therapy, revalidation and peri-operative care. Indirect non medical costs are defined as the total costs due to loss of productivity measured by the time back to work.

Secondary endpoints are total postoperative hospital stay in days, including hospital stay ofpatients who are readmitted within 30 days after surgery and quality of life and health status after 6 weeks, 3 months and one year after surgery. Quality of life and health status will be measured by two validated questionnaires; Short Form 36 (SF-36) and the WHOQOL-100. Further secondary endpoints are complications and mortality within 30 days after surgery, readmission rates, time back to work and differences in surgical-oncological radicality between open and laparoscopic surgery.

### Participating centers

Five Dutch hospitals including one university medical centre en four general teaching hospitals, comparable by size and expertise, will enroll patients.

### Study population

The study population consists of all patients with colon carcinoma, eligible for surgical treatment within the study period January 2007 to July 2010.

Inclusion criteria are: patients with a primary colon carcinoma, over 18 years of age, ASA I en II, who give informed consent.

Exclusion criteria are: pregnancy, ASA III-IV, previous abdominal surgery and metastasized illness.

### Ethics

This study is conducted in accordance with the principles of the Declaration of Helsinki and 'good clinical practice' guidelines. All collected data will be kept confidential at all times. The independent medical ethics committees of all participating hospitals have approved the study protocol. Prior to inclusion, written informed consent will be obtained from all patients.

The proposed cohort study carries no additional risks, as extra diagnostics or other than established treatment methods will not be used.

### Study outline

Inclusion and informed consent is obtained at the outpatient clinic. The patient is presented the appropriate treatment modality according to the current cohort, after which informed consent for that specific treatment is obtained.

Patients assigned to cohort 2 and 3 with ERAS recovery will receive additional information about the ERAS program by an ERAS nurse and an anesthesiologist prior to hospital admittance. All patients in cohort 2 and 3 will be admitted to a ward, were nurses and medical staff are trained in the ERAS program, and the ERAS protocol used is checked by the project experts.

Patients included into the third cohort will be operated by an experienced laparoscopic surgeon. The requirement for surgeons to perform laparoscopic colon surgery is 20 completed procedures.

To accomplish standardization and quality of care of the participating hospitals, prior to the start of the study every clinic is visited and agreements will be made on peri-operative care and the surgical procedures. For cohort 1 a protocol which defines traditional/conventional care will be uses by every hospital. Before cohort 2, an ERAS-expert panel visits the hospitals to check and agree upon the ERAS elements used in the clinic. A minimum number of 8 ERAS elements or more will be considered as ERAS peri-operative care. Before cohort 3, a quality control assessment will be performed in every hospital by experts on laparoscopic colon surgery, also accomplishing standardization of the laparoscopic methods used.

### Discharge criteria

Whether the discharge criteria are met will be assessed and scored on every postoperative day. Discharge criteria include adequate pain control with oral analgesics, no nausea and ability to take solid foods, intestinal passage of flatus and/or stool, mobilization and self support as comparable to the preoperative level, agreement of the patient.

### Statistical analysis

#### Intention to Treat

The analysis will be performed in accordance with the intention to treat principle.

#### Sample size calculation

We used an extensive table to calculate all direct medical costs including overhead and consultant costs for open and laparoscopic colon surgery for an average Dutch hospital. The main cost differences were due to the difference in operating time, use of (disposable) laparoscopic instruments and hospital stay. Based on our costs calculation, for each patient the difference in direct medical costs between laparoscopic colectomy en open colectomy is 2967 euro (38%). Considering approximately 9000 colon carcinoma operations performed annually in the Netherlands http://www.prismant.nl, the hypothetical direct costs of all 'open' colectomies performed are 38.7 million euro. The hypothetical direct costs of laparoscopically colectomies for the Netherlands are 65.3 million euro. Performing all colectomies in the Netherlands by a laparoscopic technique would result in 26.7 (= 38%) euro extra direct costs compared to performing all colectomies by the open technique.

Power calculation of the study

p1 (direct medical cost of laparoscopic colon surgery in the Netherlands) = 100 %

p2 (direct medical cost of open colon surgery in the Netherlands) = 62%

alfa = 0.01, beta = 0.05, f = 17.8

Based on differences of approximately 2000 euro found in literature form other countries, the number needed in each group would be n = 43. Therefore a more conservative trial size of 3 × 40 = 120 patients is taken into account.

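### The 38% cost difference behind the power calculation cannot be reconciled with the national totals printed beside it, which give 41% of laparoscopic cost or 69% above open cost

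*Protocol article*

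**What the plan says.** Under Sample size calculation, the protocol article puts the direct medical cost difference between laparoscopic and open colectomy at 2,967 euro per patient and labels it 38%. It scales costs to about 9,000 operations a year, with 38.7 million euro for open surgery. For the alternative, "The hypothetical direct costs of laparoscopically colectomies for the Netherlands are 65.3 million euro". Moving entirely to laparoscopy, it says, "would result in 26.7 (= 38%) euro extra direct costs compared to performing all colectomies by the open technique"; the word million is evidently missing.

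The power inputs follow: "p1 (direct medical cost of laparoscopic colon surgery in the Netherlands) = 100" per cent, "p2 (direct medical cost of open colon surgery in the Netherlands) = 62" per cent, and "alfa = 0.01, beta = 0.05, f = 17.8". No sample size is printed for this 38% difference. The one per-group number given, 43, is tied to a difference of about 2,000 euro taken from foreign literature. The plan then settles on 40 per group.

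Two other places use the same figures. The Abstract (Method/design) justifies the 120 patients by the 38% difference. The Background (Health care problem) gives 38.6 million for open surgery and describes the literature as "showing an increase to 65.3 million euro for laparoscopic surgery (difference of 26.7 million euro per year".

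**The concern.** The percentage and the totals stand side by side and describe the same contrast, yet they do not agree. The sentence names open surgery as the comparator, and open surgery is the study's control cohort, so a reader will take 38% as the increase over control. The printed totals imply a much larger increase.

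The mismatch also reaches the power calculation. The value p2 = 62% is 38% restated, whereas the totals give a different p2. Any sample size that starts from a cost in one arm then depends on which of two sets of costs was used. The planned 40 per group lies between the two answers for the plan's 2,000 euro scenario.

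**Working it through.** **Inputs** (Sample size calculation unless noted): difference 2,967 euro per patient, labelled 38%; 9,000 operations; totals 38.7 million open (38.6 under Health care problem) and 65.3 million laparoscopic; difference 26.7 million; p1 = 100%, p2 = 62%; f = 17.8; second scenario 2,000 euro with n = 43; planned 40 per group.

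**1. The absolute difference agrees.** 2,967 × 9,000 = 26.70 million. By subtraction, 65.3 − 38.7 = 26.6 and 65.3 − 38.6 = 26.7, which is rounding. The conflict is therefore in the base cost, not in the difference.

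**2. The percentage does not agree.**
- Relative to open: 26.7/38.7 = 69.0% (26.7/38.6 = 69.2%).
- Relative to laparoscopic: 26.7/65.3 = 40.9%.
- p2 from the totals: 38.7/65.3 = 59.3%, against 62% stated.

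The ratio of two national totals does not depend on the number of operations, so the approximate 9,000 cannot explain this.

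**3. Two cost bases.**

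| | Implied by 38% of laparoscopic cost | Implied by the totals |
|---|---|---|
| Laparoscopic, per patient | 2,967/0.38 = 7,808 | 65.3 million/9,000 = 7,256 |
| Open, per patient | 7,808 − 2,967 = 4,841 | 38.7 million/9,000 = 4,300 |
| Totals at 9,000 (million) | 70.3 and 43.6 | 65.3 and 38.7 |
| Excess over open | 2,967/4,841 = 61% | 2,967/4,300 = 69% |

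Rounding of 38% does not bridge the gap. At 37.5% the open cost is 2,967/0.375 − 2,967 = 4,945 euro; at 38.5% it is 2,967/0.385 − 2,967 = 4,739 euro. Neither is near 4,300.

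**4. Reproducing n = 43.** The article prints no formula. The value f = 17.8 equals (2.576 + 1.645)², so alpha is two-sided. The unpooled two-proportion formula is

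n = f × [p1(1 − p1) + p2(1 − p2)]/(p1 − p2)².

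With p1 = 1 this reduces to n = f × p2/(1 − p2), which is f × open cost/difference. Adding 2,000 euro to each open cost:
- Open 4,841: 17.8 × 4,841/2,000 = 43.1, which matches the stated 43.
- Open 4,300: 17.8 × 4,300/2,000 = 38.3, so 39.

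Subtracting 2,000 euro from the laparoscopic cost instead gives 17.8 × 5,808/2,000 = 51.7 and 17.8 × 5,256/2,000 = 46.8. Neither matches, which supports the first reading.

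**5. The 2,967 euro difference on the same formula.** 17.8 × 0.62/0.38 = 29.0 with p2 = 62%, and 17.8 × 38.7/26.6 = 25.9 with p2 from the totals. The article prints neither number. Pooled variants, one- or two-sided and with or without continuity correction, give 31 to 40 for p2 = 62%.

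**The case against.** The strongest reply is that the base is declared. Laparoscopic cost is set to 100% and open cost to 62%, so 38% is a share of laparoscopic cost. Like for like, the discrepancy is then 38% against 41%, about three points. Most of the distance from 38% to 69% is a change of denominator, since even the costs that fit 38% put laparoscopy 61% above open. This stands, and it means that 69% should not be set against 38% as though both were on the same base. It does not rescue the sentence that expresses the excess relative to open surgery, which is wrong on either cost base. Nor does it remove the three-point conflict.

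A reader might infer more: that p2 = 62% and n = 43 are wrong and that 59% is correct. The documents do not support that. The stated 43 reproduces on the costs that 38% implies, so the national totals may be the faulty side; the underlying cost table is not shown.

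A reader might also take 38% as the only effect size in the plan. The 2,000 euro scenario is a second one, and the printed 43 belongs to it; 38% enters there only through a back-calculated open cost.

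Finally, the effect on sample size is modest, and moving to the totals reduces it. That is correct.

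**Conclusion.** The inconsistency is established from printed figures alone: 38% (p2 = 62%) against 41% of laparoscopic cost (p2 = 59%) or 69% above open cost. The sentence giving 38% extra compared with open surgery is wrong whichever base is used; the excess is 61% or 69%. Which cost base is in error cannot be decided from this article.

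The consequence for sample size is conditional on the inferred formula and on adding 2,000 euro to the open cost. On those assumptions the 2,000 euro scenario needs 43 per group on one base and 39 on the other, so whether the planned 40 meets it depends on the unreconciled base. For the 2,967 euro difference, 40 is enough on either base under the same formula (29 or 26). It would go too far to conclude that the study is too small because of this slip: correcting towards the totals lowers the required number. The correction should still be made, because the abstract rests the trial size on the 38%.

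**What to change.** Take one pair of per-patient costs, open and laparoscopic, from the cost table. From that pair recompute the national totals, the percentage with its base named, p2, and n for both the 2,967 euro and the 2,000 euro differences. State the formula, and say which n the planned 40 is meant to satisfy.

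Reword the sentence that compares with the open technique so that its percentage is relative to open cost, and supply the missing million. If the printed totals are kept, this reads 69% above open (41% of laparoscopic cost) with p2 = 59%. If the 38% is kept, the totals become about 43.6 and 70.3 million and the excess over open is 61%.

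Bring the Abstract, Health care problem and Sample size calculation into line, including 38.6 against 38.7 million. The cost is a recalculation and some rewording; the correction itself changes nothing in the conduct of the study.

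### The 95% power claim rests on mean costs recoded as percentages with no standard deviation, so it is unsupported for a primary endpoint measured in euros

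*Protocol article*

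**What the plan says.** Under Primary and secondary endpoints, the protocol article states: "The primary endpoint of the Tapas-study are costs, both direct medical en indirect non medical costs". Direct medical cost is an amount in euros for each patient, and the sample size section treats it so when it says that "the difference in direct medical costs between laparoscopic colectomy en open colectomy is 2967 euro (38"%).

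The same section then lists its power inputs. They are "p1 (direct medical cost of laparoscopic colon surgery in the Netherlands) = 100"%, "p2 (direct medical cost of open colon surgery in the Netherlands) = 62"% and "alfa = 0.01, beta = 0.05, f = 17.8". No formula is named, and no SD, coefficient of variation or other measure of between-patient spread appears anywhere in the article.

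Two group sizes follow. One is "Based on differences of approximately 2000 euro found in literature form other countries, the number needed in each group would be n = 43". The other is the size adopted: "Therefore a more conservative trial size of 3 × 40 = 120 patients is taken into account". The abstract repeats the claim: "alfa = 0.01, beta = 0.05), a group size of 3×40 = 120 patients is calculated".

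**The concern.** The figures 100% and 62% are two mean costs, each divided by the laparoscopic mean. They are not the shares of patients who had some event. The labels p1 and p2 together with the multiplier f belong to the usual comparison of two proportions, where the variance comes from p(1 − p). Applied here, that variance is 1 × 0 = 0 for laparoscopic surgery and 0.62 × 0.38 = 0.2356 for open surgery. Neither value says anything about how much costs differ between patients. The result would be the same whether costs varied by 100 euro or by 10,000 euro.

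The study is meant to inform whether hospitals should invest in laparoscopic theatres and ERAS programmes. A reader who trusts 95% power may take a non-significant cost difference as evidence of equal cost. The printed calculation gives no ground for that inference.

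**Working it through.** **Inputs from the sample size section.** p1 = 1.00, p2 = 0.62, alpha 0.01, beta 0.05, f = 17.8; differences of 2,967 and about 2,000 euro; 40 per group; national totals of 38.7 and 65.3 million euro for about 9,000 operations. The SD of cost is not given and is assumed below.

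**1. The multiplier.** f = (z₀.₉₉₅ + z₀.₉₅)² = (2.576 + 1.645)² = 17.8. This reproduces and shows that alpha is two-sided; a one-sided alpha would give 15.8.

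**2. The group size of 40 from p1 and p2.**
- Simple form: n = f[p1(1 − p1) + p2(1 − p2)]/(p1 − p2)² = 17.8 × 0.2356/0.1444 = 29.0.
- Pooled form, with mean proportion 0.81: n = [2.576√(2 × 0.81 × 0.19) + 1.645√0.2356]²/0.38² = (1.429 + 0.798)²/0.1444 = 34.4, so 35.
- Pooled form with continuity correction: (34.4/4)[1 + √(1 + 4/(34.4 × 0.38))]² = 39.4, so 40.

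One standard binomial variant therefore lands on the adopted size. The simple form does not.

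**3. The group size of 43 for about 2,000 euro.** The article implies two possible laparoscopic base costs: 65.3 million/9,000 = 7,256 euro, and 2,967/0.38 = 7,808 euro.

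| Base (euro) | 2,000/base | Simple | Pooled | Pooled, corrected |
|---|---|---|---|---|
| 7,256 | 0.276 | 46.8 | 53 | 60 |
| 7,808 | 0.256 | 51.7 | 58 | 65 |

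None gives 43. A base that the article does not state, 4,300 + 2,000 = 6,300 euro (where 4,300 = 38.7 million/9,000), gives 44 with the pooled form, which is close but not equal.

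**4. A calculation suited to the endpoint.** For two means, n per group = 2f(SD/difference)². As an example, SD 3,000 and difference 2,000 give 2 × 17.8 × 1.5² = 80.1, so 81. Power at 40 per cohort uses the noncentral t distribution with 78 degrees of freedom, two-sided alpha 0.01 and noncentrality (difference/SD)√(40/2). The half-width of a 99% confidence interval is 2.640 × SD × √(2/40).

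| Assumed SD (euro) | n for 2,000 | Power at 40, 2,000 | n for 2,967 | Power at 40, 2,967 | 99% CI half-width (euro) |
|---|---|---|---|---|---|
| 2,000 | 36 | 96% | 17 | >99% | 1,181 |
| 3,000 | 81 | 63% | 37 | 96% | 1,771 |
| 4,000 | 143 | 35% | 65 | 75% | 2,362 |
| 5,000 | 223 | 20% | 102 | 51% | 2,952 |

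Solving the same power function for 95% gives a largest admissible SD of about 2,070 euro for a 2,000 euro difference and about 3,075 euro for 2,967 euro. The n columns use the normal approximation, which is slightly more favourable; by that route the two limits would be about 2,120 and 3,145 euro.

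**The case against.** The article names no formula, so the binomial calculation is an inference. The multiplier f would serve a comparison of means equally well. The figure of 43 is not recovered from proportions on the article's own base costs, whereas a two-means formula would give it at an SD of about 2,000 × √(43/35.6) ≈ 2,200 euro. An SD may therefore have been used for that figure and may stand in a fuller protocol.

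This stands as a limit on what can be said about 43. It does not rescue the printed calculation. The listed inputs are cost percentages labelled p1 and p2, a means formula cannot be run from them, and one binomial variant gives exactly the 40 adopted. A fuller document could add an SD, but it could not make a ratio of mean costs a proportion of patients.

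A reader might also infer that the study is too small, or that correcting the calculation must lower its power. The documents support neither. At an SD of 2,000 euro, 40 per cohort gives about 96% power for 2,000 euro. For the article's own 2,967 euro difference, power is still 96% at an SD of 3,000 euro.

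Finally, the article states no rule that a non-significant result will be read as equal cost. That remains a risk of interpretation and is not a planned decision.

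**Conclusion.** The point holds in this form: the stated beta of 0.05 at alpha 0.01 does not follow from the printed inputs for a continuous cost endpoint, in the sample size section or in the abstract. The error is one of method, since f itself is computed correctly. That a two-proportion formula was used is a strong inference and not stated text, and the origin of 43 remains unexplained.

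Whether 40 per cohort is enough cannot be settled from the article. It turns on whether the SD of per-patient cost lies below about 2,070 euro (for 2,000 euro) or about 3,075 euro (for 2,967 euro). These limits assume equal SDs in the two cohorts, approximately normal mean costs, and a single pairwise comparison at two-sided alpha 0.01. The SD range of 2,000 to 5,000 euro is an assumption. Because this calculation is the only printed support for the size of the study, it should be corrected.

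**What to change.** Delete the p1/p2 calculation and keep 3 × 40. In the sample size section and the abstract, replace the power statement with a two-means calculation in euros, n = 2f(SD/difference)², naming the SD and its source. Over a stated range of SDs, give the power or the detectable difference for 40 per cohort, together with the expected confidence-interval width. If 43 is retained, state the formula and inputs behind it.

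State also that cost differences will be reported with confidence intervals, so that a non-significant result is not read as equal cost.

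The change is to wording only and needs no extra patients. Its price is that the power claim becomes conditional on an assumed SD and may turn out below 95%.

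### The sample size treats the 40 patients per cohort as independent although programmes are switched by hospital and period, so the stated beta = 0.05 is unsupported and probably optimistic

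*Protocol article*

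**What the plan says.** Under Participating centers, the protocol article names "Five Dutch hospitals including one university medical centre en four general teaching hospitals". Study design assigns each programme its own period, one after the other. Under Study outline no patient is allocated individually: "The patient is presented the appropriate treatment modality according to the current cohort". The same section has every hospital apply the conventional-care protocol in cohort 1 and undergo a laparoscopic quality assessment ahead of cohort 3. For the second programme it says: "Before cohort 2, an ERAS-expert panel visits the hospitals to check and agree upon the ERAS elements used in the clinic". The fair reading is that all five hospitals pass through all three programmes in the same order.

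Sample size calculation enters mean costs as if they were proportions: "p1 (direct medical cost of laparoscopic colon surgery in the Netherlands) = 100" per cent and "p2 (direct medical cost of open colon surgery in the Netherlands) = 62" per cent. The error rates and multiplier are "alfa = 0.01, beta = 0.05, f = 17.8". The abstract repeats these error rates for a 38% difference and concludes that "a group size of 3×40 = 120 patients is calculated". Neither place mentions hospital, period, an ICC or a design effect.

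**The concern.** Patients treated in one hospital during one period share theatre, ward team, the local set of ERAS elements, surgeons and cost prices. The article itself names operating time, disposables and hospital stay as the main sources of cost difference. It accepts any set of 8 or more ERAS elements and requires 20 completed procedures of a laparoscopic surgeon, so programme content and experience can differ between hospitals and between periods. Costs within a hospital-period may therefore be correlated, and 40 patients would then carry less information about a programme contrast than 40 independent patients.

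The study is meant to justify or reject hospital investments. A null result credited with 95% power at the 1% level could be given more weight than it deserves. A significant result from a pooled comparison could be a false positive more often than 1% of the time.

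**Working it through.** **Inputs.** From the article: two-group sizing with alpha 0.01, beta 0.05, f = 17.8; p1 = 1.00, p2 = 0.62; 40 per cohort; 5 hospitals; 3 periods. Assumed, because the article gives no value: equal recruitment, and a hospital-period ICC (ρ) of 0.02, 0.05 or 0.10.

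**1. Reproduce the multiplier.** (z₀.₉₉₅ + z₀.₉₅)² = (2.576 + 1.645)² = 17.81. This matches f = 17.8, two-sided, and contains no clustering term.

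**2. Reproduce the group size.** The article does not say which formula it used. Three standard versions, all for independent patients, give:
- simple f formula: 17.8 × (0 + 0.62 × 0.38) / 0.38² = 17.8 × 0.2356 / 0.1444 = 29.04;
- pooled two-proportion formula: 35;
- pooled with continuity correction: 40, the stated figure.

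So 40 is reached with a design effect of exactly 1. Whether it contains slack depends on the formula, and both ends are carried forward: 40 as the exact requirement, and 29 as the requirement.

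**3. Layout.** 5 × 3 = 15 hospital-periods, with m = 40/5 = 8 patients in each. A hospital-by-period test has (5 − 1) × (3 − 1) = 8 df.

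**4. Design effect.** For contrasts within hospital, DE = 1 + (m − 1)ρ_within − m·ρ_between, where ρ_between is the part that stays constant in a hospital across periods. With no stable part, DE = 1 + 7ρ, which is 1.14, 1.35 and 1.70. The effective size is 40/DE = 35.1, 29.6 and 23.5 per cohort.

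**5. Power.** Noncentrality is λ = λ₀/√DE. If 40 is exactly what is needed, λ₀ = √17.81 = 4.221. By the f formula at 38%, λ₀ = 0.38 / √(0.2356/40) = 4.951. Normal-quantile power is Φ(λ − 2.576). The 8-df power uses the noncentral t with critical value 3.355.

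| ρ | DE | 40 exact: normal | 40 exact: 8 df | f formula: normal | f formula: 8 df |
|---|---|---|---|---|---|
| 0 | 1.00 | 95% | 77% | 99% | 90% |
| 0.02 | 1.14 | 92% | 71% | 98% | 86% |
| 0.05 | 1.35 | 85% | 62% | 95% | 78% |
| 0.10 | 1.70 | 75% | 50% | 89% | 67% |

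The ρ = 0 row separates two effects. With 40 as the exact requirement, the 8-df test alone lowers power from 95% to 77%. A hospital-period ICC of 0.05 then lowers it from 77% to 62%, or from 95% to 85% on normal quantiles.

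**6. Cancellation of stable hospital differences.** With ρ_within = 0.05 and 40 as the exact requirement:
- ρ_between = 0.04: DE = 1 + 0.35 − 0.32 = 1.03, power 94% (normal) or 76% (8 df);
- ρ_between = 0.05: DE = 0.95, power 96% or 80%.

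**7. Error rate of a pooled patient-level test.** Approximately 2 × [1 − Φ(2.576/√DE)] = 1.6%, 2.7% and 4.8% for ρ = 0.02, 0.05 and 0.10. Simulation of t-tests on 5 hospitals × 8 patients per cohort gave 2.6% at 0.05 and 5.0% at 0.10.

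**The case against.** A reader might infer that the design definitely misses 95% power. The documents do not support that. By the f formula at 38% only 29 per cohort are needed, so 40 tolerates a design effect of 40/29.04 = 1.38, or an ICC of (1.38 − 1)/7, about 0.054. On normal quantiles power at an ICC of 0.05 is still 95.4%. This stands as far as it goes, but it relies on one of several possible formulas and on normal quantiles. With 8 df the same case gives 78%.

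It is also tempting to take the n = 43 for about 2000 euro as the baseline. That brings in a different fault: against 43, 40 patients give 93.2% with no clustering at all. The figures here therefore do not start from it.

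The table's lower figures put the whole ICC into the hospital-period. Theatre and surgeons may be stable features of a hospital, the hospitals are described as comparable, and expert visits aim to standardise care. All of this may make hospital-by-period variation small, and step 6 shows that the loss on normal quantiles is then small too. The article offers no figure to show that it is.

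Finally, the article commits to no particular test beyond intention to treat, and an analysis plan that is not shown may hold a suitable model. The inflated error rate is thus a warning against a pooled analysis, not a charge that one is planned. A later model would not, however, repair a power statement already printed on the basis of independent patients.

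**Conclusion.** The point holds in a limited form. The sizing assumes independent patients, the programmes are assigned by hospital-period, and no allowance connects the two. The beta = 0.05 at alpha 0.01 in the abstract and in Sample size calculation is therefore unsupported and probably optimistic.

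The size cannot be fixed from the document. For assumed hospital-period ICCs of 0.02 to 0.10, power runs from 92% down to 75% (normal) or 71% to 50% (8 df) if 40 is the exact requirement, and from 98% to 89% or 86% to 67% by the f formula at 38%. These ranges assume 8 patients per hospital-period and no cancelling stable component. They also inherit the article's treatment of costs as proportions: without a cost SD, power for the real endpoint cannot be verified.

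Two other matters are separate and would remain after this correction: the confounding of programme with calendar period, and the choice of 40 after a calculated 43.

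**What to change.** Keep 3 × 40.

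1. In the abstract and in Sample size calculation, replace the unconditional beta = 0.05 with power over a stated range of assumed hospital-period ICCs, naming the effect size and the test to which each figure refers.
2. Base the primary cost contrasts on within-hospital comparisons that allow for hospital-by-period variation, with small-sample degrees of freedom. Examples are a model with hospital as a fixed effect and a hospital-by-period random term, or a two-way analysis of the 15 hospital-period mean costs. Do not rest them on a pooled comparison of three groups of 40. If the analysis plan already does this, a cross-reference is enough.

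The cost is wording and one model term. No extra patients are needed, and the only added data items, hospital and period, follow from where and when a patient was treated. The downside is a less favourable power figure and wider intervals.
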